### **Clinical measures analysis**

For each clinical measure (i.e., balance, gait, cognitive function, bilateral hand dexterity and strength) and for the Modified Impact Scale we will calculate the values from each time point across all phases (i.e., baseline, intervention, follow-up) and then we will evaluate the average of them, so to get a single mean value for each measure and for each phase (mean baseline; mean intervention mean follow-up). To investigate the association between the intervention protocol and clinical condition, we will calculate the differences between phases' mean values (i.e., mean baseline; mean intervention; mean follow up), reflecting to the degree of change in clinical condition following in-phase bilateral exercises.

### **Visual analysis**

Two assessors will systematically measure each outcome measure across time, inter-assessor agreement will be calculated on at least twenty percent of the data points in each condition. The minimum acceptable inter-assessor agreement will be set to 0.8 (50). Initially, a visual analysis will be conducted and presented graphically in a spaghetti plot, in order to define whether there is a functional relation between the intervention and the outcome measures (77). During the visual analysis, six features of the research design graphed data will be examined: level, trend, stability, immediacy of the effect, overlap, and consistency. Over the within-phase examination an evaluation of level, trend and stability will be examined. Level will be reported from the mean score of each dependent variable and trend will determine whether the data points

are monotonically decreased or increased. Stability will be estimated based on the percentage of data points falling within 15% of the phase median, if this is higher than 80% then we assume that this criterion is met. Additionally, over the between-phase examination an evaluation of overlapping data among baseline and intervention phases, consistency of data patterns and immediacy of effect will be performed (77). The Percentage of Non-overlapping Data index will be used to quantify the proportion of data points in the intervention phase that do not overlap with the baseline phase (86) and the test statistic will be calculated using the Improvement Rate Difference as an effect size index. Immediacy of the effect will be examined by comparing changes in level between the last three data points of one phase and the three first data points of the next phase. Furthermore, consistency of data patterns involves the observation of the data from all phases within the same condition, with greater consistency expressing greater causal relation. Each feature will be assessed individually and collectively across to all participants and to all phases. Consequently, if the intervention protocol is the sole determinant of improvement, we expect to find indicators of improvement only at the intervention phase.

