### **Study design**

Each subgroup includes five participants and each one constitutes a separate research study that follows a concurrent multiple baseline design across subjects, designed according to the 'What Works Clearinghouse' criteria for single case studies (50). During the experimental procedure, all participants will begin the study with the baseline phase at the same time while the intervention phase is introduced staggered across patients and time (see Figure 1). The intervention will be introduced systematically in one patient while baseline data collection continues in the others without any intervention. The cause-effect inference can be clearly verified by the staggered duration through separate baseline phases (51). Subsequently, if the intervention is the sole cause of improvement in participants' conditions, the proposed outcome measures will not change for the participants that remain in the baseline phase but will be improved only for those in the intervention phase.

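### The visual analysis names a spaghetti plot and six features, but none is the date-matched comparison with participants still in baseline on which the causal claim rests

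*Protocol*

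**What the plan says.** The Study design section makes each subgroup of five a separate concurrent multiple baseline study. All five begin baseline together and start the intervention at staggered times. On causation it states: "The cause-effect inference can be clearly verified by the staggered duration through separate baseline phases". The test it gives is that, if the intervention alone causes improvement, "the proposed outcome measures will not change for the participants that remain in the baseline phase", with improvement confined to those in the intervention phase. The opening design description says the same.

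The Visual analysis section sets out how the functional relation is judged. The data are to be "presented graphically in a spaghetti plot, in order to define whether there is a functional relation between the intervention and the outcome measures", and "six features of the research design graphed data will be examined: level, trend, stability, immediacy of the effect, overlap, and consistency". Three features are within-phase: "Over the within-phase examination an evaluation of level, trend and stability will be examined". The other three are between-phase:

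- Overlap compares baseline points with intervention points.
- Immediacy compares the last three points of one phase with the first three of the next.
- Consistency is described thus: "consistency of data patterns involves the observation of the data from all phases within the same condition".

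The section adds "Each feature will be assessed individually and collectively across to all participants and to all phases", and that, if the intervention is the sole cause, "we expect to find indicators of improvement only at the intervention phase". The Statistical analysis section then runs the quantitative analysis only for outcomes where the visual analysis points to an effect.

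**The concern.** A concurrent multiple baseline design guards against events that move everyone at one calendar date, such as a season or an equipment change, by checking the participants who have not yet started. The feature list does not ask for that check. The named display does not help: a spaghetti plot ordinarily overlays individuals on one set of axes, and the section does not say whether time runs by calendar or from each person's start, or whether each phase change is marked. If time ran from each person's start, the concurrent baselines would no longer line up.

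At stake is whether a shared calendar event could be carried forward as a functional relation, although data already collected would show that participants still in baseline moved too.

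**Working it through.** **Features against the causal test.** The protocol gives no figure to reproduce here, so the first step is to set the text side by side.

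| Feature | What is compared | Starter against those still in baseline, same date? |
|---|---|---|
| Level, trend, stability | points within one phase | no |
| Overlap | baseline and intervention points | no |
| Immediacy | last three and first three points of adjacent phases | no |
| Consistency | phases of the same condition | no |

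**Comparisons available.** There are five participants per subgroup (Study design). Assume that they start one at a time. Those still in baseline at successive starts number 4, 3, 2, 1 and 0. The check is therefore available at four of five starts, with 4 + 3 + 2 + 1 = 10 pairings per outcome and subgroup.

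**What a shared shift would look like.** The schedule is in a figure not shown, so it is assumed:

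- starts at weeks 4, 6, 8, 10 and 12;
- weekly baseline points from week 1 to the week before the start (3, 5, 7, 9 and 11 points);
- five intervention points (the number is in TMS measures analysis) three weeks apart from the start;
- no treatment effect and no noise;
- one shared step of size 1, in the direction of improvement, from week 8.

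Phase-mean difference = (share of intervention points at or after week 8) − (share of baseline points at or after week 8). Non-overlap is the share of intervention points above every baseline point. Immediacy is the mean of the first three intervention points minus the mean of the last three baseline points.

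| Start week | Phase-mean difference | Non-overlap | Immediacy |
|---|---|---|---|
| 4 | 3/5 − 0/3 = 0.60 | 60% | 1/3 − 0 = 0.33 |
| 6 | 4/5 − 0/5 = 0.80 | 80% | 2/3 − 0 = 0.67 |
| 8 | 5/5 − 0/7 = 1.00 | 100% | 1 − 0 = 1.00 |
| 10 | 5/5 − 2/9 = 0.78 | 0% | 1 − 2/3 = 0.33 |
| 12 | 5/5 − 4/11 = 0.64 | 0% | 1 − 1 = 0.00 |

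The mean phase difference is (0.60 + 0.80 + 1.00 + 0.78 + 0.64)/5 = 0.76 of the step. All five show a positive level difference with no treatment effect. Only the participant who starts at week 8 shows it in full.

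**Other schedules.** Take equally spaced points, baselines of 3–7, 5–9 or 3, 5, 7, 9, 11 points, five intervention points, and the step at any one of the five starts. The five-participant mean then runs from (0 + 0 + 0.20 + 0.60 + 1)/5 = 0.36 to (0.80 + 1 + 0.857 + 0.75 + 0.667)/5 = 0.81. In every case non-overlap is 0% for those who start after the step.

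**Whether the stability rule catches it.** The rule wants more than 80% of points within 15% of the phase median. In the week-8 example the last two starters have 7/9 = 78% and 7/11 = 64% of baseline points at the old level. A step larger than 15% of the median would make both miss the criterion. A step of 15% or less leaves every point inside the band, so both would meet it. The section does not say what follows for the functional relation when the criterion is missed.

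**The case against.** Three arguments on the other side carry weight.

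- **The staggering already disperses a shared event.** It can coincide with at most one start if participants start one at a time. In the example, non-overlap runs 60, 80, 100, 0 and 0%, and immediacy is at most 0.67 outside the coinciding participant. A careful reader would see a discordant pattern. This stands, and it rules out a reading that someone might reach: that a shared event biases every participant by its full size. What remains is that no stated rule says such a pattern fails, while the level feature and the phase-mean differences still point towards improvement in everyone.
- **The logic is in the document.** The design text states the expectation, and the visual analysis refers to collective assessment and to improvement only in the intervention phase. This stands in part. Assessing the same six features collectively is still not a comparison at a given date, and an expectation is not a criterion.
- **The plot does not decide alone, and layout may be left to an analysis plan.** Several features are numerical and do not depend on the graph. A reader might also infer that the stagger cannot be read from a spaghetti plot. The documents do not support that: baselines begin together, so five lines on a calendar axis with marked starts could show it. But the protocol itself fixes both the display and the list of features, so the missing comparison is not merely a detail left for later.

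Some threats are also reduced by other provisions: one investigator reads all latencies, procedures are the same at all time points, and outside influences are monitored. These do not cover season.

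**Conclusion.** The point holds in this form: the step that decides the functional relation uses a poorly suited, under-specified display and six features, none of which is the date-matched comparison that the design gives as its basis for cause and effect.

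The size depends on any shared shift and on the schedule. With a step at week 8 in the assumed schedule, the apparent change in phase means is 1.00 of the step in one participant and 0.60 to 0.80 in the other four. Across the other schedules examined, the five-participant mean is 0.36 to 0.81 of the step. These figures assume a single noise-free step in the direction of improvement, one start at a time and no treatment effect. They illustrate the mechanism and do not predict that such a shift will occur.

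The later quantitative analysis does not clearly repair this. It runs only on outcomes that the visual step passes, its null hypothesis concerns baseline versus intervention, and it states no calendar-time comparison. The change is worth making before data are read, because it makes the stated causal test operational with data that will exist anyway.

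**What to change.** In the Visual analysis section:

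1. Replace the spaghetti plot by stacked panels, one per participant (and one per side for outcomes measured bilaterally), on a common calendar axis with each participant's own phase-change lines.
2. Add a criterion to the six features: a start counts as a demonstration of effect only if the participant who starts shifts and those still in baseline do not shift at that date. Define beforehand what counts as a shift, using the points on either side of the date.
3. State that, with participants starting one at a time, the criterion applies to the first four starts and that the fifth has no remaining concurrent baseline.

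The cost is a different graph layout and one stricter criterion, under which some apparent effects may no longer count. No new data are needed.

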## **Analysis plan**

To investigate possible effects of our protocol we will follow recommended guidelines (77), in which we will perform a separate analysis for each of the outcome measures, in all experimental phases (i.e., baseline, intervention and follow up). We will perform a visual analyses first, in order to determine whether there is a functional relationship between the intervention and the outcome measures, and secondly, we will perform a quantitative analysis methods to evaluate the magnitude of the intervention effect, provided there is evidence from the visual analyses (77). We will perform all neurophysiological and clinical assessments to each participant according to the number of data points during each phase (i.e., baseline, intervention, follow up) (see Figure 1).

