For both upper limbs, all neurophysiological measures (i.e., rMT, MEP amplitude, latency) will be first calculated from each MEP trace and then averaged to get a single value. These calculations will be done according to the different time points for each participant in the baseline phase, at five time points in the intervention phase and at three time points in the follow-up phase (see Figure 1). In order to investigate possible changes in cortical excitability, we will measure rMT and peak-to-peak amplitude throughout assessing MEPs (80) of the Abductor Pollicis Brevis muscle, while measuring of latency will indicate possible changes in CMCT. Any changes in all measures across time points, will indicate alterations in corticospinal plasticity (81). We will evaluate resting motor threshold using MTAT 2.0 (64) (available at <http://clinicalresearcher.org/software.htm>) and to investigate possible changes in individual corticospinal plasticity of each participant, we will calculate bilaterally the difference between the mean values of each phase (82,83). On the other hand, from each stimulus response during the suprathreshold stimulation (i.e., 120% of rMT) (81), we will calculate offline the MEP peak-to-peak amplitude and latency. To define CMCT (ms), we will subtract the peripheral conduction time ((F wave latency + M wave latency – 1)/2) from the CMCT (MEP latency). The F wave is the muscle response elicited by activation of the alpha motor neuron, while the M wave is the direct response of the muscle (84). A prolonged CMCT indicates damage of large fibres, demyelination of central motor pathways or slow summation of descending excitatory potentials in the corticospinal tract evoked by TMS (84,85). To standardise all latencies (i.e., MEP, F and M wave), we will use a visual inspection from stimulation onset to response onset, performed from the same investigator so to ensure reliability of the study across all time points. To define possible changes in CMCT, we will evaluate bilaterally the difference between the mean values of each phase.

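### With five or three points per phase, the strict 80% stability cut-off tolerates no outlying point, and its flat-median band can score within-phase change as instability

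*Protocol*

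**What the plan says.** The Visual analysis section of the protocol examines six features: "level, trend, stability, immediacy of the effect, overlap, and consistency". Stability belongs to the examination within phases: "Over the within-phase examination an evaluation of level, trend and stability will be examined". Its measure and its pass mark are fixed together: "Stability will be estimated based on the percentage of data points falling within 15% of the phase median, if this is higher than 80" per cent, the criterion counts as met. The inequality is strict. The rule is not confined to baseline, because "Each feature will be assessed individually and collectively across to all participants and to all phases".

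The section TMS measures analysis gives the number of neurophysiological assessments: "at five time points in the intervention phase and at three time points in the follow-up phase". The number of baseline points differs between participants and is not given in the text. For all assessments, the Analysis plan section refers to Figure 1, which is not shown ("according to the number of data points during each phase").

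The visual analysis then acts as a gate. Under Analysis plan and Statistical analysis, the quantitative analysis is run only for outcomes where the visual analysis points to a functional effect. Statistical analysis describes these outcomes as the ones showing a trend, and includes piecewise regression to capture the effect over time as well as the immediate effect.

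**The concern.** A reader takes an 80% criterion to mean that some scatter is allowed. With five or three points and a strict inequality, none is. The nominal 80% rule becomes a 100% rule in the two phases whose lengths the protocol states for its primary measures. It loosens once a phase has six points, so two participants with equal measurement noise but different staggered baseline lengths can be held to different standards.

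The second difficulty is the centre of the band. A response that builds over the 12 weeks of exercise moves the first and last points away from the phase median. The trend feature, and the later choice of piecewise regression, look for that kind of change, while the stability feature can score it as a failure. Stability is also the only one of the six features with a stated numerical pass mark. Without a rule for what a failed pass mark means, the weight it gets can be decided after the data have been seen.

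**Working it through.** **Inputs from the protocol.** Band: within 15% of the phase median. Cut-off: strictly more than 80% of the points (Visual analysis). Points per phase: 5 in intervention and 3 in follow-up, stated for the TMS measures (TMS measures analysis). The plan reports no computed figure on this point, so there is none to reproduce.

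**Inputs assumed.** The protocol gives no within-phase variability and no expected size of within-phase change. Illustrative values: CV of 5% to 20%, and a linear rise of 20% to 40% of the starting value.

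**Step 1: how many points must comply.** The smallest k with k/n > 0.80, against k/n ≥ 0.80:

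| n | largest share with one miss | k needed, >80% | k needed, ≥80% |
|---|---|---|---|
| 3 | 2/3 = 66.7% | 3 | 3 |
| 4 | 3/4 = 75.0% | 4 | 4 |
| 5 | 4/5 = 80.0% | 5 | 4 |
| 6 | 5/6 = 83.3% | 5 | 5 |

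At n = 5, the zero tolerance comes from the strict inequality alone. At n = 3, it comes from the number of points, and changing the inequality does not help.

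**Step 2: flat phase, noise only.** Simulated probability that a phase without trend is called stable (log-normal errors, at least 200,000 phases per case):

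| CV (assumed) | n = 3, either wording | n = 5, >80% | n = 5, ≥80% | n = 6, either wording |
|---|---|---|---|---|
| 5% | 0.98 | 0.98 | 1.00 | 1.00 |
| 10% | 0.69 | 0.51 | 0.89 | 0.86 |
| 15% | 0.42 | 0.19 | 0.60 | 0.49 |
| 20% | 0.27 | 0.08 | 0.37 | 0.26 |

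At CV 10% under the current wording, the probability is 0.51 with five points and 0.86 with six. Normal errors give nearly the same values (0.51 at CV 10% and 0.19 at 15%, n = 5).

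**Step 3: linear gain without noise.** Take five equally spaced points from 1 to 1 + r. The median is 1 + r/2, and the end points lie r/2 from it. They leave the band when r/2 > 0.15 × (1 + r/2), that is, when 0.85 × r/2 > 0.15, or r > 0.30/0.85 = 0.353. The limit is therefore about 35% of the starting value, which is 30% of the median. Both end points leave together, so the share drops from 5/5 to 3/5 = 60%. For example, 1.0, 1.1, 1.2, 1.3, 1.4 has a band of 1.02 to 1.38 and scores 60%. Without noise, the choice between >80% and ≥80% makes no difference here.

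**Step 4: linear gain with noise, CV 5%, n = 5.** Probability of being called stable:

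| Rise from first to last point | as % of median, r/(1 + r/2) | >80% | ≥80% |
|---|---|---|---|
| 20% | 18% | 0.65 | 0.96 |
| 30% | 26% | 0.29 | 0.80 |
| 40% | 33% | 0.07 | 0.51 |

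With no trend, the same noise gives 0.98 under the current wording. The fall from 0.98 to 0.65 and 0.29 is due to the trend, at sizes that would pass if there were no noise.

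**The case against.** The strongest reply is that nothing in the text follows from an unstable phase. Stability is one of six features weighed together, and no sentence says that failing it rejects a functional relation or blocks an analysis. Trend is examined in its own right, and Statistical analysis selects outcomes that show one, so a steady gain may itself open the gate. To call such a phase not flat around its median is an accurate description.

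Most of this stands, and it limits the point. A reader might infer that real progressive training effects are generally classed as unstable and so count against the intervention. The protocol does not support that: a smooth gain of up to about 35% of the starting value passes, and no penalty is attached to failing. A reader might also infer that MEP amplitude can hardly ever pass while latency nearly always does. That needs a CV for each measure. The protocol gives none, and each MEP value is the average over 25 stimuli, so the relevant CV is that of a session mean. Finally, the five and three points are stated for the neurophysiological measures only; carrying them over to the clinical measures is an assumption.

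The reply does not remove the problem in the rule itself. A numerical criterion has been fixed, it applies in all phases, and it feeds the judgement that decides which outcomes are analysed further. That failing it has no stated meaning adds to the ambiguity.

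**Conclusion.** The point holds in limited form, and the plan should be changed. The counting result is exact for the TMS measures: with five or three points, every point must lie within the band, whereas six points allow one miss.

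The practical size depends on assumed variability. At a CV of about 5%, a flat five-point phase is hardly affected (0.98). At 10%, about half of such phases fail (0.51 pass), and at 15% about four in five fail (0.19 pass). For a gradual response, the flat-median band alone causes failure only above about 35% of the starting value. With a CV of 5%, failure is already common at rises of 20% (0.65 pass) and 30% (0.29 pass).

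The result is a threshold that does not do what its stated percentage suggests, and a band that pulls against the trend the protocol itself looks for. The documents do not show that a real effect would be lost or that the study's conclusions would be invalid.

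**What to change.** In the Visual analysis section:

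1. Word the cut-off as at least 80%. In a five-point phase this allows one outlying point (0.89 instead of 0.51 at CV 10%). It changes nothing in the three-point follow-up, where all three points are still needed.
2. Use the criterion around the flat phase median for baseline, where it shows that the participant is steady before the intervention starts.
3. In intervention and follow-up, judge scatter around the fitted phase trend. With only three follow-up points, report this as description, without a pass mark.
4. Say in one sentence how a failed stability criterion enters the overall visual judgement.

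The cost is a few sentences of text, slightly more analysis work and a more lenient stability label. No new data are needed. Bands specific to each measure are an option, but they need test-retest figures from outside the protocol and are not part of the required change.

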### **Statistical analysis**

For each of the outcome variables that the visual analysis indicates a potential functional effect, a quantitative analysis will be performed to estimate the effect size. This analysis will be performed for each variable at which a significant trend is shown as described in the previous section. In order to estimate the individual-level effect sizes, we will use three different methods, as suggested by 'What Works Clearinghouse' (50), the standardized mean difference (Cohen's  $d$ ), the standardized mean difference with correction for small sample sizes (Hedges'  $g$ ) and piecewise regression analysis which does not only reflect the immediate intervention effect, but also the intervention effect across time. Multilevel modelling, which is recommended by the 'What Works Clearinghouse' and the single case educational design, specific mean difference index will be used to estimate the magnitude of the effect across cases and compared to the effect obtained by the single level estimates (77). For all the different neurophysiological parameters and clinical conditions, evaluated separately, the null hypothesis is that "there is no improvement from the proposed intervention", thus participants' responses are independent from the condition (baseline versus intervention) under which they were observed. The alternative hypothesis is that "the neurophysiological parameters and /or the clinical condition of the participants will be affected by the specific intervention", again assessed separately. We will reject the null hypothesis if the  $p$  value is smaller than 0.05. All tests will be two sided. Statistical analyses will be performed using the statistical software R (<https://www.r-project.org/>).

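### The overlap index chosen (PND) falls on average as the baseline lengthens, so its values are not comparable between participants whose baselines differ in length by design

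*Protocol*

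**What the plan says.** The Visual analysis section of the protocol lists six features to be examined: level, trend, stability, immediacy, overlap and consistency. For overlap it fixes two indices. The first is PND: "The Percentage of Non-overlapping Data index will be used to quantify the proportion of data points in the intervention phase" that do not overlap with baseline. The second is IRD: "the test statistic will be calculated using the Improvement Rate Difference as an effect size index". The section gives neither a cut-off nor a no-effect value for either index, and makes no allowance for baseline length. It then says: "Each feature will be assessed individually and collectively across to all participants and to all phases".

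Under Study design, "Each subgroup includes five participants", all start baseline together, and "the intervention phase is introduced staggered across patients and time". Baseline length therefore differs between participants by construction. TMS measures analysis confirms this: values are calculated "according to the different time points for each participant in the baseline phase", but "at five time points in the intervention phase and at three time points in the follow-up phase".

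The visual analysis has a consequence. Under Statistical analysis: "For each of the outcome variables that the visual analysis indicates a potential functional effect, a quantitative analysis will be performed". The Analysis plan section sets the same condition.

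**The concern.** PND measures every intervention point against the best value seen in baseline. The more baseline points there are, the more extreme that best value tends to be, and the harder it is to exceed. In a design where all participants have the same baseline length this would matter little. Here baseline length is the very thing that is varied, and the inference rests on seeing the effect repeated across the staggered starts. An index that drifts with baseline length can make a real effect look weaker in later starters for a reason unrelated to their response. Overlap is one input to the judgement on whether an outcome is analysed quantitatively at all.

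The second index raises a separate question. A reader who sees an effect size normally takes zero to mean no effect, and IRD does not behave that way.

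**Working it through.** The protocol states no expected value for PND or IRD, so there is no figure of its own to reproduce.

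**Inputs**
- Intervention points per participant: n = 5 (TMS measures analysis; assumed the same for the clinical measures).
- Baseline points per participant: m, differing between participants. The counts are in Figure 1, which is not shown. I assume m = 3 to 9, extended to 12 where noted.
- Data model: exchangeable points without trend or ties for the no-effect case; independent normal data for a shift. Improvement is in one known direction.

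**PND with no effect.** An intervention point is non-overlapping if it is the largest among itself and the m baseline points. Under exchangeability that has probability 1/(m+1), so mean PND = 1/(m+1). Enumerating all rank orders of m + 5 points gives the same values.

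**PND with a shift of d SD.** Mean PND = ∫ Φ(x)^m φ(x − d) dx, evaluated numerically.

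**NAP.** This is the share of all baseline–intervention pairs in which the intervention point is better. Its mean is Φ(d/√2), which does not contain m: Φ(0) = 0.50 and Φ(0.707) = 0.76.

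| Baseline points m | Mean PND, no effect | Mean PND, 1 SD shift | NAP, no effect | NAP, 1 SD shift |
|---|---|---|---|---|
| 3 | 1/4 = 25% | 55% | 0.50 | 0.76 |
| 5 | 1/6 = 16.7% | 45% | 0.50 | 0.76 |
| 7 | 1/8 = 12.5% | 39% | 0.50 | 0.76 |
| 9 | 1/10 = 10% | 34% | 0.50 | 0.76 |

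From 3 to 9 baseline points the drift is 25 − 10 = 15 percentage points with no effect, and 55 − 34 = 21 with a 1 SD shift. At 2 SD, mean PND falls from 82% (m = 3) to 67% (m = 9).

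**Sensitivity.** With first-order autocorrelation of 0.6 and no effect, mean PND falls from 31.8% (m = 3) to 11.4% (m = 12), so the pattern does not depend on independence. If points outside the baseline range on either side were counted, the no-effect mean would be 2/(m+1), with the same drift.

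**IRD with no effect.** IRD is built from R, the minimum number of points that must be removed to eliminate overlap. Two variants were enumerated with n = 5.
- Robust form, removals split equally between phases: IRD = 1 − R/(2n) − R/(2m).
- Original form, using the actual removals: (1 − b/n) − a/m, where a baseline and b intervention points are removed. A range is given where several minimal solutions tie.

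| m | Robust IRD, mean | Original IRD, mean |
|---|---|---|
| 3 | 0.376 | 0.24–0.33 |
| 5 | 0.306 | 0.306 |
| 8 | 0.326 | 0.20–0.26 |
| 12 | 0.365 | 0.12–0.18 |

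Over m = 3 to 12 the robust mean lies between about 0.31 and 0.38. The original form lies between about 0.12 and 0.33 and falls as baselines lengthen beyond five points.

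**The case against.** The strongest case on the other side has five parts.

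1. **Size.** With five intervention points, one point is worth 20 percentage points of PND. The no-effect drift of 15 points is less than one observation, and the 21 points at 1 SD is about one. The SD of PND between series at 1 SD is 27 to 31 points over m = 3 to 9, so the drift is modest beside chance variation in any one participant. This stands: the statement is about averages, and a given later starter can still have the higher PND.
2. **Direction of harm.** A longer baseline makes PND stricter. It costs sensitivity in later starters and does not add false positives there. This stands.
3. **Weight in the decision.** Overlap is one of six features, and the effect sizes in the Statistical analysis section (Cohen's d, Hedges' g, piecewise regression, multilevel model) use neither PND nor IRD. This stands. A reader might infer that the visual analysis has an inflated or computable error rate. The protocol sets no cut-off, so none follows. Interpretive benchmarks may also be in an analysis plan that is not shown, so their absence is not held against the protocol.
4. **IRD.** A reader might infer that IRD makes overlap non-comparable in the same way, or that it always averages about 0.3 by chance. Neither is supported. The robust form is nearly flat across baseline lengths; only the original form drifts materially, and to well below 0.3 with long baselines. The protocol does not say which is meant. What remains is that neither form centres on zero.
5. **Preference.** PND is an established index, cited in the protocol. That is fair as to PND in general. It does not answer the mismatch with a design that varies baseline length on purpose and then judges features collectively.

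**Conclusion.** The point holds for PND. Its mean depends on baseline length, and baseline length differs between participants by design, so average PND values are not comparable across them. The direction of the drift follows from the definition of the index. Its size rests on the assumed 3 to 9 baseline points, five intervention points in every outcome, and independent normal data for the shifted case.

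The practical effect is reduced sensitivity for later starters in one component of the visual judgement. It is not a demonstrated error in the decision to proceed to quantitative analysis. The IRD note is secondary: an index described as the test statistic has a non-zero no-effect mean that depends on an unnamed variant, so a moderate value could be misread as improvement. This is a worthwhile, inexpensive improvement to a method choice and not a contradiction in the plan.

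**What to change.** In the Visual analysis section, make NAP, or Tau = 2×NAP − 1, with its standard error the overlap index for judgements between participants, and keep PND as a descriptive figure only. If IRD is kept, name the variant and print beside each value its no-effect mean for that participant's phase lengths.

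The cost is a sentence or two in the protocol and a few lines of R, which the protocol already specifies, on data already planned. The downsides are that familiar PND cut-offs can no longer be quoted and that IRD will look less favourable next to its chance level.
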